#### Inclusion criteria:

Participants fulfilling all the following inclusion criteria are eligible for the study:

- female or male sex,
- aged between 40 and 60 years,
- body mass index between 25.0 and 34.9 kg/m^2,
- sedentary lifestyle, defined as not meeting the WHO guidelines on PA, i.e., at least 150 minutes of moderate-intensity aerobic PA per week as well as muscle-strengthening activities on two or more days per week (28),
- medical clearance for HIIT by a study physician (including vital sign evaluation, clinical examination, resting and exercise ECG),
- informed consent as documented by signature.

#### Exclusion criteria:

Participants fulfilling one of the following exclusion criteria will not be included in the study:

- known pregnancy or breastfeeding,
- any current exercise-limiting musculoskeletal conditions of the lower limbs,
- any known current or chronic conditions limiting exhaustive exercise,
- known diabetes mellitus of any type,
- dyslipidaemia, if pharmaceutically treated,
- arterial hypertension  $\geq 160/100$  mmHg, pharmaceutically treated or not,
- any other known cardiovascular disease,
- known NASH,
- known macular degeneration, glaucoma, or high intraocular pressure ( $\geq 20$  mm Hg),
- particular diet (vegetarian, vegan, lactose-free, gluten-free, or FODMAP-low diet (fermentable oligosaccharides, disaccharides, monosaccharides, and polyols),
- intake of glucagon-like peptide-1 analogues, orlistat or any weight-loss drug,
- inability to follow the procedures of the study, e.g., due to linguistic or cognitive problems,
- concomitant involvement in another interventional trial or participation in another interventional trial in the last four weeks.

### **3.2 Recruitment, screening, and informed consent procedure**

Inhabitants from the Basel area will be invited to participate in this study via advertisements in local newspapers and on diverse social media channels. A similar recruitment process was successful for the EXAMIN AGE and HyperVasc studies (54, 82). Suitable patients of the Exercise Medicine Clinic of the DSBG will also be offered to participate.

The investigators will explain during a phone call the nature of the study, its purpose, the procedures involved, the expected duration, the potential risks and benefits, and any discomfort it may entail to each potential participant. The inclusion and exclusion criteria will be explained to each potential participant. Each participant will be informed that participation in the study is voluntary and that they may withdraw from the study at any time without reason.

Following the phone call, all potential participants will be provided via e-mail with a participant information sheet and a consent form describing the study and providing sufficient information for participants to make an informed decision about their participation in the study. Participants will be given at least 24h (after receiving the participant information sheet and consent form) to decide whether to participate. The recruitment will be continuous until the targeted 98 participants are enrolled. The formal consent of a participant, using the approved consent form, will be obtained before the participant is submitted to any study procedure. The study participant will receive a copy of the signed informed consent. The consent form will be retained as part of the study records.

The study will be conducted in accordance with the Declaration of Helsinki.

Potential participants will be screened for initial eligibility in a first personal visit at the Department of Sport, Exercise and Health of the University of Basel, which will take place after potential participants return the signed consent form. Inclusion and exclusion criteria will be carefully reviewed during the first personal visit by asking the questions in the document “Fragen Screening” point-by-point. A clinical assessment (including vital sign evaluation, clinical examination, height and weight measurement, body mass index (BMI) calculation, resting and exercise ECG) and medical clearance will also take place during this first visit. Eligible participants will then be invited to a baseline assessment.

### **3.3 Study procedures**

#### First contact by phone – study information:

The investigators will telephone each potential participant to explain the nature of the study, its purpose, the procedures involved, the expected duration, the potential risks and benefits, and any discomfort it may entail. The inclusion and exclusion criteria will be explained to each potential participant. Each participant will be informed that participation in the study is voluntary and that they may withdraw from the study at any time without reason.

#### 1st visit – clinical and eligibility assessment:

A clinical assessment which includes vital sign evaluation (blood pressure, heart rate, respiration rate, oxygen saturation, and body temperature), physical examination, height and weight measurement, and BMI calculation, will be conducted. Habitual PA will be assessed using the Global Physical Activity Questionnaire (57, 58).

A resting and exercise ECG will be realised to screen for cardiac contraindications to maximal exertion. Maximal cardiopulmonary exercise testing (CPET) will be conducted on a cycle ergometer to determine  $\text{VO}_{2\text{peak}}$ , peak heart rate and power output (Ergoselect 200; Ergoline, Bitz, Germany). Finally, medical clearance will be given during this first visit.

The screening for eligibility will consist of the inclusion and exclusion criteria assessment (see section 3.1 for inclusion and exclusion criteria). Participants successfully passing this screening will be invited for a baseline assessment. Instructions for the further procedures of the study will be given.

#### 2nd visit – collection of standardised meals

Each participant will collect, at least three days before the baseline assessment, standardised, pre-packaged meals for the two days preceding blood sampling to minimise potential confounding. Depending on the delay between the first visit and the baseline assessment, this second visit can be combined with the first visit.

#### 3rd visit – baseline assessment

Body composition will be analysed before and after the intervention by DXA and bioelectrical impedance analysis. Trained medical staff will draw blood samples by venepuncture of the cubital fossa following an overnight fast pre-and post-intervention. Retinal vessel diameters, a novel surrogate of microvascular health which responds positively to exercise intervention, will be assessed pre-and post-intervention as extensively described by Hanssen et al. (65). Brachial artery flow-mediated dilatation (FMD) reflects endothelial function as an early marker of atherosclerotic arterial damage (68). It provides an in vivo, noninvasive, direct measure of artery function and health (69). Echocardiographic strain analysis of the atria offers insights into cardiac mechanical adaptation in response to elevated sphingolipid levels (83).

#### Intervention (8-week HIIT vs. PA recommendations)

The exercise intervention will consist of a supervised HIIT (two walking- and one indoor cycling-based session weekly), starting with a habituation week at an intensity of 75% of the maximal heart rate (HRmax). In the following seven weeks, the participants will perform a HIIT based on the following protocol and for a total duration of 45 min per session (modified from Wisløff et al. (50)): warm-up for 10 min at 60%–70% HRmax followed by a high-intensity interval consisting of 4×4 min at 80%–95% HRmax with 3 min of active recovery at 60%–70% HRmax and a 10 min cool-down at 60%–70% HRmax. Heart rate will be monitored during training by Garmin HRM-Dual heart rate sensors combined with Garmin Forerunner 45S watches. Exercise scientists motivate the participants during the intervals and will control each participant's heart rate during and after every training session. This protocol was chosen because it fulfils the requirements of a high-volume HIIT (51), has been extensively studied in both healthy and clinical populations, and its effects on CRF improvement are well-documented (39, 52). In addition, it has been previously used by our research group, with high adherence and absence of drop-out observed in healthy participants and patients with cardiovascular risk factors (53, 54). The control group will get PA recommendations based on current guidelines (56). The control group participants will get a phone call after four weeks to enquire about their well-being.

#### 4th visit – collection of standardised meals

Each participant will collect, at least three days before the baseline assessment, standardised, pre-packaged meals for the two days preceding blood sampling at post-intervention assessment to minimise potential confounding. For the intervention group, this visit can be combined with a training session.

#### 5th visit – post-intervention assessment

After completing the 8-week intervention, the same measurements from the baseline assessment will be repeated (including vital sign evaluation, clinical examination, height and weight measurement, BMI calculation, resting and exercise ECG). A second CPET will be performed to verify that the exercise intervention effectively improved CRF. Habitual PA will be re-assessed using the Global Physical Activity Questionnaire (57, 58).

All blood samples will be stored at -80°C at the Department of Sport, Exercise and Health of the University of Basel before being delivered to the Metabolomics Unit of the Faculty of Biology and Medicine at the University of Lausanne. A high-coverage method using reversed-phase liquid chromatography coupled to tandem mass spectrometry (RPLC-MS/MS) will be applied to quantify the 61 circulating sphingolipids (48).

[figure not shown]

**Figure 4: Schedule and sequence of study procedures as planned for study visits.** Abbreviations: ECG = electrocardiogram, CPET = cardio-pulmonary exercise testing, HIIT = high intensity interval training

### 3.4 Withdrawal and discontinuation

Every participant enrolled in the study will always be able to withdraw his participation for further assessments without any reason. Already collected data will remain available for data analysis. Participants will be removed from the study if exclusion criteria are encountered during the study or if participants withdraw informed consent.

## 4. STATISTICS AND METHODOLOGY

### 4.1 Statistical analysis plan and sample size calculation

The sample size calculation and statistical analysis plan of the SphingoFIT study has been developed in close collaboration with [name], advising statistician at the DSBG. The sample size calculation is based on the four primary endpoints, which are also the species entering the ceramide score (i.e., ceramide 16:0, ceramide 18:0, ceramide 24:0 and ceramide 24:1) (24, 25). It was hypothesised that 1) log2-transformed pre-intervention sphingolipid levels are similar in both the intervention and the control groups and 2) the standard deviation of log2-transformed sphingolipid levels correspond to 0.475 (which is the average standard deviation obtained for the four sphingolipids mentioned above in participants of the COMplete Health study aged 40-60 years (84)). As the results of the SphingoHIIT study are not available yet, the effect size was estimated based on the unique intervention study available in the literature (35). The authors of this study reported an average effect size (expressed as a geometric mean ratio) of 1.17. This means that the geometric mean of the sphingolipid levels was 1.17 times higher in control than in the intervention group following the exercise intervention. Assuming a realistic correlation coefficient  $\rho$  of 0.6 between pre-and post-intervention values for sphingolipid levels, an analysis of covariance (ANCOVA) was used to calculate the sample size. A result of 49 participants per group for a power of 80% was obtained (Figure 4). Notably, a drop-out rate of 10% was considered in the sample size calculation (55).

[figure not shown]

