### Statistical analyses:

An ANCOVA will be run for each sphingolipid species to estimate the effect of the intervention (85). The post-intervention sphingolipid value will be the dependent variable. In contrast, the pre-intervention sphingolipid value, a group variable (i.e., intervention or control group) and all control variables will be the independent variables. To identify control variables to be included in the models, we drew a causal-directed acyclic graph (DAG) using DAGitty (86). Age, sex, body fat mass and CRF were identified as variables to be included in the models to reduce the outcome variation and improve the precision of the average causal effect of the intervention (87). The design will control food intake (as each participant will receive individualised, pre-packaged meals for the two preceding blood sampling) and PA. Graphical methods will be used to assess the normal distribution of data. If the data are not normally distributed, sphingolipid concentrations will be log-transformed. The Benjamini-Hochberg method will adjust P-values for multiple testing (88). The significance level is set at  $\alpha = 0.05$ ; all tests will be two-sided. All analyses will be done according to the intention-to-treat principle. Statistical analyses will be conducted using R (version 4.0.2 or later). The study will report its results in compliance with the CONSORT statement (89).

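### The 49 per group and 80% power hold for one species at an unadjusted two-sided 0.05, but the plan adjusts P-values by Benjamini-Hochberg over a family it does not name

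*Protocol*

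**What the plan says.** The sample-size paragraph of Protocol section 4.1 rests on the four primary ceramides (16:0, 18:0, 24:0 and 24:1). Its inputs are:

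- spread: "the standard deviation of log 2 -transformed sphingolipid levels correspond to 0.475";
- effect: the one available intervention study "reported an average effect size (expressed as a geometric mean ratio) of 1.17";
- pre-post correlation: "of 0.6 between pre-and post-intervention values for sphingolipid levels";
- attrition: "a drop-out rate of 10% was considered in the sample size calculation".

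With ANCOVA as the method, the result is "A result of 49 participants per group for a power of 80% was obtained (Figure 4". The paragraph gives no significance level and does not mention multiplicity.

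The analysis paragraph in the same section says: "An ANCOVA will be run for each sphingolipid species to estimate the effect of the intervention (85". It sets a two-sided 5% level and adds: "The Benjamini-Hochberg method will adjust P-values for multiple testing (88". It does not say which P-values are adjusted together. Section 2.2 names the four ceramides as primary endpoints and places 57 other sphingolipids among the secondary endpoints, so 61 species are tested in all. The protocol does not say how many of the four primaries must be significant for the trial to succeed.

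**The concern.** When a BH family holds more than one P-value, the adjusted values are never smaller than the raw ones. If the 49 per group was derived at a raw 0.05, the planned test is stricter than the one that was powered, and the quoted 80% describes a test that will not be the basis of the conclusion.

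The missing family definition adds to this. BH within four P-values and BH over 61 P-values can give different answers for the same primary ceramide. If the choice is left until the results are known, it could change the primary conclusion.

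**Working it through.** **Inputs from section 4.1.** Log2 SD 0.475, geometric mean ratio 1.17, correlation 0.6, power 80%, drop-out 10%, two-sided 0.05 (the last from the analysis paragraph).

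**Step 1: reproduce the 49.**

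- Difference on the log2 scale: log2(1.17) = 0.2265.
- ANCOVA residual SD: 0.475 × √(1 − 0.6²) = 0.475 × 0.8 = 0.380.
- n per group = 2 × (1.960 + 0.8416)² × 0.380² / 0.2265² = 44.18.
- With drop-out: 44.18 / 0.9 = 49.1, which matches the stated 49.

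**Step 2: look for a multiplicity allowance.** The same formula at stricter levels gives:

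| Two-sided level | n per group | n / 0.9 |
|---|---|---|
| 0.05 | 44.2 | 49.1 |
| 0.025 | 53.5 | 59.4 |
| 0.0125 (0.05/4) | 62.8 | 69.7 |

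Other variants also miss 49 (rounded up before and after drop-out): one-sided 0.05 gives 35, then 39; a change-score analysis gives 56, then 63; post-values only give 70, then 78. The 49 contains no allowance for multiplicity.

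**Step 3: fixed-level power with the evaluable sample.** 49 × 0.9 = 44.1, so 44 per group. The noncentrality is 0.2265 / (0.380 × √(2/44)) = 2.796. Noncentral-t power (85 degrees of freedom) is 78.9% at 0.05, 69.6% at 0.025 and 59.7% at 0.0125. The normal approximation gives 79.8% at 0.05 and runs one to two points higher throughout.

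**Step 4: per-species power under BH.** Simulated with t statistics and 44 per group. The documents do not give the between-species correlation (assumed common, 0 to 0.8), the number of responding species, or the effect in each responder (assumed 1.17). Ranges are over the correlation.

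| Family | Scenario | Power per responding primary |
|---|---|---|
| None (unadjusted) | – | about 79% |
| Four primaries | all four respond | about 74-76% |
| Four primaries | two respond | about 66-67% |
| Four primaries | one responds | about 60% |
| All 61 | four primaries, no secondary | about 34% |
| All 61 | four primaries, a quarter of secondaries | about 52-54% |
| All 61 | four primaries, half of secondaries | about 59-64% |
| All 61 | four primaries, all 57 secondaries | about 69-75% |

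**Step 5: power for the set of four.** Under BH within four, with all four responding, at least one is significant in about 80-98% of trials and all four in about 40-65%. A power figure is therefore only meaningful if it says what it counts.

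**Step 6: strictest step.** At 0.05/4, the log2 difference detectable with 80% power is (2.498 + 0.842) × 0.380 × √(2/44) = 0.271, a ratio of 2^0.271 = 1.21.

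**The case against.** Four points can fairly be made for the plan.

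- **The family may be the four primaries.** Section 2.2 separates primary from secondary species, and the sample size is based on the four. BH within four is at least as natural a reading as BH over 61, and an analysis plan not shown here might fix it. This stands. A reader might infer from the uniform wording of the analysis paragraph that the four primary P-values are ranked together with the 57 secondary ones, so that the primary result hangs on the secondary species. The protocol does not say so. The figures for 61 species are conditional on that reading.
- **Under BH within four the loss is small.** If all four respond, as the calculation presumes, it is about 3 to 5 points. This also stands. Covariates beyond baseline could recover some of it, but the protocol gives no figure for their contribution. The 60% case needs three primaries not to respond, which the protocol does not assume.
- **Without a success rule, the overall power may lie above or below 80%.** This is correct, and it is why any restated figure must be labelled per species.
- **BH targets the false discovery rate.** A reader might infer that error on the primaries is uncontrolled. That is too strong: with one family of 61 the chance of a false primary claim would vary with the secondary response, but only on a reading the document does not state.

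None of this restores the 80%, since every family of two or more adjusted P-values is stricter than the test that was powered. The sample-size figure is not shown, so a significance level printed there could not be checked; the inputs in the text reproduce 49 at an unadjusted two-sided 0.05.

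**Conclusion.** The point holds as a mismatch between two statements within section 4.1. The 80% is unadjusted per-species power, whereas the planned P-values are BH-adjusted. On the reading most favourable to the plan (four primaries, all responding at 1.17), per-species power falls from about 79% to about 74-76%; it falls further to about 60% if only one responds. The much lower figures, down to about 34%, apply only if the unnamed family is taken to be all 61 species, which the protocol neither states nor excludes. The reproduction of 49 rests wholly on the protocol's inputs. The BH figures also rest on the assumed correlations, numbers of responders and common effect size.

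**What to change.** In section 4.1:

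1. State that BH is applied within the four primary species and, separately, within the 57 secondary species.
2. State that 80% is unadjusted power for a single species.
3. Restate the per-species power under BH within four, with its assumptions: 44 evaluable per group, ratio 1.17, between-species correlation 0 to 0.8; about 74-76% if all four respond, falling to about 60% if only one does.
4. Optionally add that the ratio detectable with 80% power at the strictest step (0.05/4) is about 1.21. This is a worst-case bound, not an equivalent of the figures in item 3.

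The cost is a few sentences and a slightly less favourable stated power. The sample size, data collection and conduct do not change. The family should be fixed before group comparisons are seen.

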**Figure 5: Sample size calculation**

[figure not shown]

**Figure 6: Directed acyclic graph representing the effect of HIIT on sphingolipid levels and other influencing variables.** Abbreviations: HIIT = high-intensity interval training, CRF = cardiorespiratory fitness, PA = physical activity, SL = sphingolipid levels.

### Statistical analyses:

An ANCOVA will be run for each sphingolipid species to estimate the effect of the intervention (85). The post-intervention sphingolipid value will be the dependent variable. In contrast, the pre-intervention sphingolipid value, a group variable (i.e., intervention or control group) and all control variables will be the independent variables. To identify control variables to be included in the models, we drew a causal-directed acyclic graph (DAG) using DAGitty (86). Age, sex, body fat mass and CRF were identified as variables to be included in the models to reduce the outcome variation and improve the precision of the average causal effect of the intervention (87). The design will control food intake (as each participant will receive individualised, pre-packaged meals for the two preceding blood sampling) and PA. Graphical methods will be used to assess the normal distribution of data. If the data are not normally distributed, sphingolipid concentrations will be log-transformed. The Benjamini-Hochberg method will adjust P-values for multiple testing (88). The significance level is set at  $\alpha = 0.05$ ; all tests will be two-sided. All analyses will be done according to the intention-to-treat principle. Statistical analyses will be conducted using R (version 4.0.2 or later). The study will report its results in compliance with the CONSORT statement (89).

## 4.2 Handling of missing data and drop-outs

A complete case analysis will be done if the proportion of missing data is below 5%. Otherwise, we will consider multiple imputations. A drop-out rate of 10% was considered in the sample size calculation.

## 5. REGULATORY ASPECTS AND SAFETY

### 5.1 Local regulations / Declaration of Helsinki

This study will be conducted in compliance with the protocol, the current version of the Declaration of Helsinki, the ICH-GCP, the HRA, as well as other locally relevant legal and regulatory requirements.

### 5.2 (Serious) Adverse Events and notification of safety and protective measures

An Adverse Event (AE) is any untoward medical occurrence in a study participant which does not necessarily have a causal relationship with the trial procedure. An AE can therefore be any unfavourable or unintended finding, symptom, or disease temporally associated with a trial procedure, whether related to it or not.

A Serious Adverse Event (SAE) (ClinO, Art. 63) is any untoward medical occurrence that:

- Results in death or is life-threatening,
- Requires in-patient hospitalisation or prolongation of existing hospitalisation, or
- Results in persistent or significant disability or incapacity

The investigator and Sponsor-Investigator make a causality assessment of the event to the trial intervention (see table below based on the terms given in ICH E2A guidelines). Any event assessed as possibly, probably or related is classified as related to the trial intervention.

| Relationship | Description |
|--------------|-------------|
|--------------|-------------|

|                                                                                         |                                                                                                                           |
|-----------------------------------------------------------------------------------------|---------------------------------------------------------------------------------------------------------------------------|
| Definitely                                                                              | Temporal relationship
Improvement after dechallenge*
Recurrence after rechallenge
(or other proof of drug cause) |
| Probably                                                                                | Temporal relationship
Improvement after dechallenge
No other cause evident                                          |
| Possibly                                                                                | Temporal relationship
Other cause possible                                                                             |
| Unlikely                                                                                | Any assessable reaction that does not fulfil the above conditions                                                         |
| Not related                                                                             | Causal relationship can be ruled out                                                                                      |
| *Improvement after dechallenge only taken into consideration, if applicable to reaction |                                                                                                                           |

Both Investigator and Sponsor-Investigator make a severity assessment of the event as mild, moderate, or severe. Mild means the complication is tolerable, moderate means it interferes with daily activities and severe means it renders daily activities impossible.

